# Premature ejaculation in primary care: communication strategies versus usual care for male patients consulting for a sexual, urogenital or psychological reason – GET UP: study protocol for a cluster randomised controlled trial

**DOI:** 10.1186/s13063-018-2947-2

**Published:** 2018-11-12

**Keywords:** Premature ejaculation, General practice, Sexual dysfunction

## Abstract

**Background:**

Premature ejaculation (PE) is the most common sexual dysfunction among men. According to patients, the general practitioner (GP) is the appropriate professional with whom to discuss this issue. However, few patients receive the medical help needed because GPs find it difficult to talk to their patients about sex. A previous qualitative study provided six strategies described by GPs who had tackled the topic during consultation. A pilot study showed that using one of these strategies after a training course led to an increase in the rate of consultations where the topic was raised: an increase from 6.6 to 30.8%. The aim of this study is to compare whether training in communication skills with these six strategies is more effective than usual care on the incidence of patients bringing up the topic of PE with their GP.

**Methods:**

A cluster randomised controlled trial, stratified over four areas comparing an intervention group, which will receive the six strategies training session, and a control group, which ensures routine medical care. The primary outcome is to investigate the efficacy of a training in communication skills directed towards this pathology, compared with usual care procedures, on the incidence of patients bringing up the topic of PE with their GP. The secondary objective relates to the variation in the quality of life of patients after having recently addressed the topic of PE. Quality of life will be evaluated using the SF-12 health scale, with scoring filled in by the patient immediately after the consultation and 4 weeks later. The patients suffering from PE will be identified if their score is higher than 9 on the Premature Ejaculation Diagnostic Tool filled in 4 weeks after the consultation. The number of patients necessary to highlight a significant difference between the two groups from 5 to 20% is 101. Therefore, a total of 600 patients is expected, 300 in each arm (40 GPs, 15 patients per GP; risk *α* = 5%; power = 90%; intra-cluster correlation coefficient *ρ* = 0.2; Hawthorne effect = 15%; lost-to-follow-up rates for GPs = 10% and for patients = 20%).

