### Feasibility

As far as we are aware, this interventional multicentre study will be the first one concerned with PE in the area of primary health care. We created a pilot intervention study in primary care in order to estimate the feasibility of such a study design, as well as the incidence of diagnosed PE with, and without, the use of strategies. Thirteen GPs agreed to participate in the IG, six of whom included their patients in the study. Twenty-four GPs participated in the CG, 13 of whom included their patients in the study. The GPs in the IG included 26 of their patients in the study. They identified eight patients suffering from PE: 30.8%. The GPs in the CG included 61 of their patients. Among them, four were suffering from PE: 6.6% (*p* value = 0.004, OR = 6.6768, 95% confidence interval (CI) (1.55; 34.40)).

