### Sample size estimation

As this study had been designed as a cluster randomised trial, a sample size estimation was proposed which would highlight a significant difference between the two randomised groups in terms of the incidence of new cases of patients bringing up the topic of PE with their GP. It takes into account an intra-cluster correlation coefficient (ICC) varying between 0.05 and 0.20 and includes a recruitment of around 15 patients per GP [29]. In order to take into account between- and within-GP variability, expressed by intra-class correlation coefficient (ICC), this sample size must be increased by an inflation factor: 1 + (*m* − 1). ICC, with *m* the (mean) number of patients included by each GP. According to the literature [29, 30], it is not so easy to determine the appropriate value of ICC. It depends of many factors. We have chosen to fix ICC between 0.05 and 0.20, according to previous references. With 15 patients included by each GP, sample size estimation was 360 for ICC equals 0.05 and 800 for ICC at 0.20, and around 960 for ICC at 0.25. Furthermore, it is usual to observe a Hawthorne effect in this type of study. In our feasibility study, the incidence of patients who brought up PE with their GP in the CG was 6.6%. Following the guideline of PE updated by the ISSM, ‘5% of the population have an ejaculation latency of less than 2 minutes’ [8]. We estimated the incidence in the CG at around 5%. Usually in individual randomisation, *n* = 101 patients in total is necessary to highlight an absolute difference between 5 and 20%. For a two-sided type I error, *α* equals 0.05 and has a statistical power of 90%. Also, taking these aspects into account 600 patients, recruited by 40 GPs, must be included and then divided into 300 patients in each arm.

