#### Statistical methods

Analyses will be performed using Stata software, version 13 (StataCorp, College Station, TX, USA). All data will be analysed on intention to treat. The tests will be two-sided, with a type I error set at *α* = 0.05. Baseline characteristics (GPs and their patients) will be presented for each randomisation group as the mean ± standard deviation (SD) or the median (interquartile range) according to statistical distribution for continuous data and according to the number of patients and associated percentages for categorical parameters.

The comparisons between the randomised groups will be carried out using the Student *t* test or the Mann-Whitney test where appropriate, (1) normality verified by the Shapiro-Wilk test and (2) homoscedasticity by the Fisher-Snedecor test for quantitative parameters and using chi-squared or Fisher’s exact tests for categorical variables.

Outcomes will pertain to the cluster level using usual statistical tests and with more specific approaches at the individual level. Hierarchical regression models (generalised linear mixed model due to binary endpoint) will be performed as primary analysis: (1) to estimate the effect of intervention on the incidence of new cases of patients suffering from acquired and lifelong PE, natural variable PE and premature-like ejaculatory dysfunction and (2) to take into account the variability between and within, the GP cluster groups. Intra-class correlation coefficients will be presented by arm with a 95% CI. Then, GP characteristics (gender, age, geographical area) or patient characteristics (age, socioeconomic status) should be considered as covariate (fixed effects in mixed models) in adjusted multivariable analyses. The adjusted and unadjusted results will be presented: absolute numbers of patients who have raised the topic of PE with their related GP, relative risks and 95% CIs.

For secondary endpoints, comparisons at the individual level between randomised groups will be performed using an analysis of covariance for correlated data with the baseline score as a covariate, as suggested by Klar and Darlington [31] for the SF-12 quality of life scores. Results will be expressed as effect-sizes and 95% CIs. The PEDT will be analysed as a quantitative score using statistical methods described for the SF-12 quality of life and as a binary outcome (< ≥ 11) with the use of a generalised linear mixed model.

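### The 10% GP loss allowance is not reconciled with the trial's own pilot, in which 18 of 37 GPs included no patient, and the article states no allowance for such GPs

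*Protocol article*

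**What the plan says.** The Methods paragraph of the abstract fixes the design at "40 GPs, 15 patients per GP", with ICC 0.2, 90% power, a 15% Hawthorne effect and "lost-to-follow-up rates for GPs = 10% and for patients = 20" per cent. The section Sample size estimation keeps the total, saying that "600 patients, recruited by 40 GPs, must be included and then divided into 300 patients in each arm". It gives the ICC as a range from 0.05 to 0.20 and does not mention GP loss.

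The section Feasibility describes a pilot meant to show whether such a design is workable. On the intervention side: "Thirteen GPs agreed to participate in the IG, six of whom included their patients in the study". On the control side: "Twenty-four GPs participated in the CG, 13 of whom included their patients in the study". These GPs included 26 and 61 patients respectively.

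Under Recruitment, enrolment lasts 12 months, with one call and two e-mails a month to remind GPs to include patients. Under Allocation, the surgery is the unit of randomisation, GPs who share a surgery go to the same arm, and allocation is released once the GP has been recruited.

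**The concern.** The article gives two figures on how many GPs deliver data, and they are far apart: a planned 10% loss, and a pilot in which about half of the participating GPs delivered nothing. The pilot is used elsewhere in the planning, since its control rate of 6.6% is cited when the 5% assumption is set. Its experience with inactive GPs is not taken up.

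Allocation comes before patients are enrolled. A GP who enrols nobody therefore adds no patients after allocation. Analysis by intention to treat cannot use patients who were never enrolled. The planned maximum-bias and multiple-imputation analyses deal with missing outcomes of enrolled patients, so they do not help either.

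Two things are at stake. One is the expected number of patients and the power. The other is comparability: the arms attend different sessions (4 hours against 2 hours), so the GPs who become active may be selected differently in each arm.

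**Working it through.** **Inputs.** Rates of 5% and 20% (Sample size estimation: "patients in total is necessary to highlight an absolute difference between 5 and 20" per cent). Two-sided α 0.05 (Statistical methods: "The tests will be two-sided, with a type I error set at" 0.05). Target power 90% (Sample size estimation: "has a statistical power of 90" per cent). 40 GPs, 15 patients each, ICC 0.05 to 0.20, GP loss 10%. Pilot counts from Feasibility.

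**Step 1: the plan's own figure.** Pooled-variance formula for two proportions, mean rate 0.125:

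n = [1.960 × √(2 × 0.125 × 0.875) + 1.282 × √(0.05 × 0.95 + 0.20 × 0.80)]² / 0.15² = [1.960 × 0.4677 + 1.282 × 0.4555]² / 0.0225 = 100.06, rounded up to 101.

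This reproduces the article's 101, but as the number per arm and not in total. The design effect is 1 + (15 − 1) × ICC, which is 1.7 at ICC 0.05, 2.4 at 0.10 and 3.8 at 0.20. With no loss, 600 patients at ICC 0.20 give 600/(2 × 3.8) = 78.9 effective patients per arm and 82% power. The stated 90% is therefore missed at ICC 0.20 before GP loss enters. That is a separate error; the article's own requirement at ICC 0.20 is 800.

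**Step 2: pilot non-inclusion.** Intervention: 13 − 6 = 7 of 13 (54%). Control: 24 − 13 = 11 of 24 (46%). Together 18 of 37 = 48.6%, Clopper-Pearson 95% CI 31.9% to 65.6%. The lower limit is about three times 10%.

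**Step 3: effect on size and power.** For a proportion d of inactive GPs:
- active GPs = 40 × (1 − d)
- patients = 15 × active GPs
- effective n per arm = patients / (2 × design effect)
- power = Φ[(0.15 × √n − 1.960 × 0.4677) / 0.4555]

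Patient loss is ignored here.

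| Inactive GPs | Active GPs | Patients | Power, ICC 0.05 | Power, ICC 0.10 | Power, ICC 0.20 |
|---|---|---|---|---|---|
| 0% | 40 | 600 | 99% | 95% | 82% |
| 10% (plan) | 36 | 540 | 98% | 93% | 78% |
| 32% (lower CI limit) | 27.2 | 408 | 94% | 85% | 66% |
| 48.6% (pilot) | 20.5 | 308 | 87% | 73% | 53% |

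Worked case, pilot rate at ICC 0.20: 40 × 19/37 = 20.5 GPs; × 15 = 308 patients; 308/7.6 = 40.5 per arm; (0.15 × √40.5 − 0.9167)/0.4555 = 0.083; power 53%.

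**Step 4: adding the planned 20% patient loss** (12 per GP, design effect 1 + 11 × ICC). With 10% inactive GPs, 432 patients remain and power is 97%, 91% and 76% at ICC 0.05, 0.10 and 0.20. At the pilot rate, about 246 patients remain and power is 82%, 70% and 51%.

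**Step 5: over-recruitment implied.** At the pilot rate, 40 active GPs would need 40/(19/37) = about 78 GPs randomised, and 36 active GPs about 70.

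**The case against.** The strongest objection is that the two rates measure different things. The abstract speaks of GPs lost to follow-up; the pilot counts GPs who took part but included nobody. This stands, and so it would be too strong to say that the pilot contradicts the 10%. But if the 10% does not cover non-inclusion, the article states no allowance for it, although in its own pilot about half the GPs were lost that way.

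A reader might also infer that about half the clusters will vanish. The documents do not support that. Surgeries are randomised, and one with an inactive and an active GP stays in the trial, whereas the pilot counted GPs. The article does not say that the pilot was randomised, how long it ran or whether reminders were used. Twelve months of enrolment and monthly reminders may do better. For the same reason, the pilot yield of 87/19 = 4.6 patients per recruiting GP cannot be scaled to the planned 15.

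A third tempting reading is that GP inactivity is what costs the trial its 90% power. At ICC 0.20 that is wrong, since 82% is the ceiling with no loss at all. The part that belongs to this point is the drop from the 10% row to the rows below it, which is modest at ICC 0.05.

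Finally, 40 GPs may mean 40 recruiting GPs, with extra GPs provided for in the full protocol. The wording allows this, but the article does not say so. Baseline tables for GPs by arm and an attrition analysis are planned, so selection among GPs is not wholly ignored. What is not stated is that GPs without patients will be included in these.

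**Conclusion.** The point holds as a planning figure that is stated without support and not reconciled with the trial's own pilot. Going from 10% to 32% to 49% inactive GPs lowers expected patients from 540 to about 408 to about 308. Power falls from 78% to 66% to 53% at ICC 0.20, and from 98% to 94% to 87% at ICC 0.05. At ICC 0.05, even the lower confidence limit leaves power above 90%, so the consequence depends heavily on the ICC.

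These figures assume 40 GPs at the start, 15 patients per active GP, rates of 5% and 20%, no patient loss, and GPs treated as the clusters. The 49% is a pessimistic scenario, not a forecast, and should not be imposed as the planning value.

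**What to change.** 1. Justify the 10% against the pilot, for example by saying what differs in duration, reminders or choice of GPs. Otherwise replace it with a value that covers GPs who include nobody.
2. State whether 40 GPs means randomised or actively recruiting GPs. If recruiting, state how many will be randomised.
3. Restate expected active GPs, patients and power over 10% to 49% inactive GPs and ICC 0.05 to 0.20.
4. Report all randomised surgeries and GPs by arm, including those with no patient, and compare active with inactive GPs by arm using the GP data already collected.

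The cost is a less favourable stated power and minor extra reporting. Restating power does not restore it. If the trial wants to protect against the pessimistic end, it needs more GPs, and that has a real cost. Holding back allocation until a GP seems ready is not recommended as a remedy, because nothing in the article shows that it would prevent non-inclusion: the pilot's control GPs are described as participating, yet 11 of 24 included nobody.

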**Discussion:**

The implication for practice is the improvement in the quality of patient-centred care within a topic area which encompasses almost 30% of male sex-related complaints.

**Trial registration:**

ClinicalTrials.gov, ID: NCT02378779. Registered on 3 February 2015.

**Electronic supplementary material:**

The online version of this article (10.1186/s13063-018-2947-2) contains supplementary material, which is available to authorized users.

## Background

Many male patients complain about their problems with ejaculation: 21–30% of men, aged between 18 and 80, have admitted suffering from a decrease in, or loss of control of, their ejaculation [1–3]. The quality of life of the patients and their partners is impaired compared with men not suffering from premature ejaculation (PE) [4]. In addition, anorgasmia and low libido, as well as depression and anxiety, are comorbidities significantly associated with PE [5]. Defining PE is not simple: seven to ten different definitions have been proposed since 1970 [6, 7]. The definition chosen by the International Society for Sexual Medicine (ISSM) [8, 9] was an ejaculation which always, or nearly always, occurred prior to, or within about 1 min of, vaginal penetration; the inability to delay ejaculation during all or most vaginal penetrations, and negative personal consequences, such as distress, anxiety, frustration and/or the avoidance of sexual intimacy. Apart from the distinction between acquired and lifelong PE, two other categories have been described: natural variable PE and premature-like ejaculatory dysfunction [10]. Natural variable PE corresponds to the normal variation in sexual performance. The premature-like ejaculatory dysfunction corresponds to the patient’s distorted perception of time before ejaculation: the patient is convinced that he is suffering from PE although his Intravaginal Ejaculation Latency Time (IELT) is more than 1 min. While the prevalence, according to men’s self-reports, is 30%, the rate drops to 3% when the time factor is considered in isolation [5]. This statement illustrates the incompatibility between the academic definition and the actual complaints from patients.

One study showed that most of the men interviewed anonymously, in their general practitioner’s (GP’s) waiting room, considered it important to talk with their GP about their sexual concerns [11]. Almost half of them preferred that their GP initiate any discussions about sexuality. More than two thirds of the respondents would have liked their GP to signal their open-mindedness by directly addressing sexual topics during the consultation [11]. While 80% of men who participated in the study suffered at least occasionally from a reported sexual problem, only 12% had already consulted their GP about this [11]. The guideline of the ISSM emphasised the role of GPs in PE care [10]. The GP is the first medical professional that the patient meets to discuss his problem. The main objective of the GP is ‘to recognise PE and make the patient feel comfortable about getting help’ [10]. The physician-patient relationship, developed during primary care consultations, is a foundation of patient-centred care. After having identified the problem, those GPs who had good communication skills sometimes initiated treatment. However, several studies have described the difficulties reported by GPs in talking about sex. Lack of time is the most significant factor [12–14]. Sexual dysfunction is often considered to be of secondary importance after information and detection of sexually transmitted infections, contraceptive counselling, vaccinations, etc. [12–15]. In addition, it is difficult for GPs to deal with such a time-consuming topic. Feeling that they have insufficient expertise, or are ill-qualified to deal with sexual problems, are also contributing factors [13, 16]. The lack of training in sexology during their academic studies was highlighted [13, 16]. The average of 3 hours’ tuition was not sufficient to teach all the pathologies and their management [13, 16]. ‘Opening a can of worms’ is the expression often used by GPs to describe the difficulties they feel in addressing this kind of pathology during consultation [13, 16]. Factors affecting the GPs’ involvement are known: training in communication skills was the most important predictor for sexual-history taking [17].

Several types of treatment, both pharmacological and psychological, now exist and have been evaluated and recommended: PE is a treatable pathology [10, 18–21].

The first study on this topic occurred in 2009 with a qualitative study to bring to the fore the strategies used by GPs to initiate the discussion on PE. Eleven GPs participated in semi-structured interviews composed of open-ended questions for exploration and closed questions to refine the participants’ answers [22]. According to the content analysis of the interviews transcribed verbatim, six different strategies used by the GPs to tackle the subject were identified (described in the ‘Methods’ section).

The main aim of this study is to investigate whether training in communication skills with these six strategies is more effective than usual care on the incidence of patients bringing up the topic of PE with their GP.

## Methods

### Outcome

The primary outcome is the incidence of patients bringing up the topic of PE with their GP.. This was undertaken in the group where the GPs received training in communication skills directed towards this pathology, compared with the patients who received the usual care procedures.

The secondary outcome relates to the variation in the quality of life of patients after they have addressed the topic of PE as measured by the SF-12 questionnaire.

### Trial design

The GET UP trial is designed as a two-arm, randomised controlled trial with two parallel clustered groups assigned to an intervention group (IG) or a control group (CG) stratified by region (Figs. 1, 2 and 3).

**Fig. 1 Fig1:**
[figure not shown]
Study design

**Fig. 2 Fig2:**
[figure not shown]
Participant timeline

**Fig. 3 Fig3:**
[figure not shown]
Standard Protocol Items: Recommendations for Interventional Trials (SPIRIT) Schedule of study procedures

### Study setting

GPs from four French regions will participate: Brittany, Aquitaine, Massif Central, and Languedoc-Roussillon-Midi-Pyrénées. In each of the four regions, a leading investigator will be identified, to be responsible for recruitment of GPs, identification, data collection and completion of CRFs, along with following up study patients and adherence to study protocol.

The list of study sites can be obtained from the Direction de la Recherche Clinique et de l’Innovation at Brest. The GPs will not be incentivised to take part.

### Participants, interventions, and outcomes

#### Eligibility criteria

##### Patient inclusion criteria

Consecutive male patients, between 18 and 80 years old, and consulting for a sexual, urogenital or psychological reason will be included. We added age limits to the registered protocol because, above 80 years of age, the specificity of the care required for those of advanced age was out the scope of the study. A list of sexual, urogenital, and psychological reasons extracted from the International Classification of Primary Care, Second edition (ICPC -2) classification will be provided for the GPs to guide their inclusions. The GPs will inform the patient of the study after knowing the reason for the encounter, at the beginning of the consultation. The key information is written on a consent form where the study on sexual dysfunction is described and where it is explicitly written that the patient agrees to participate in the study. The patient will sign the document after he has been given the explanations. The participants will not be incentivised to take part.

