##### Patient non-inclusion criteria

Patients consulting for reasons other than sexual, urogenital or psychological will not be included. Patients consulting for one of the required reasons but who are unable to speak French, patients with psychiatric disorders affecting judgement and patients unable to sign an informed consent form were excluded.

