#### Blinding

Due to the nature of the intervention, neither the GPs from the intervention team nor the researchers recruiting the GPs can be blinded to allocation, but it will be strongly impressed upon them that they must not disclose the allocation status of the participants at the follow-up assessments. The objective of this measure is that a GP from the CG should not know that they are in a CG. An employee outside the research team will collect the questionnaires (SF-12 and PEDT) and feed data into the computer on separate datasheets so that the researchers can analyse data without having access to information about the allocation. The patients will be blinded to the allocation of their GP and the trial aim.

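### Men who consult because of premature ejaculation are eligible and appear to be events before any strategy is used, and no check is described on whether the arms enrol them alike

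*Protocol article*

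**What the plan says.** **Who is eligible** (Patient inclusion and non-inclusion criteria). "Consecutive male patients, between 18 and 80 years old, and consulting for a sexual, urogenital or psychological reason will be included". The article also says "Patients consulting for reasons other than sexual, urogenital or psychological will not be included". The other exclusions concern language, psychiatric disorders that affect judgement, and inability to consent. Neither PE as the presenting complaint nor PE already under care is listed.

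**When enrolment happens** (Patient inclusion criteria). "The GPs will inform the patient of the study after knowing the reason for the encounter, at the beginning of the consultation". GPs receive a list of qualifying reasons drawn from ICPC-2.

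**What is counted.** Under Outcome: "The primary outcome is the incidence of patients bringing up the topic of PE with their GP". Sample size estimation words it as "the incidence of new cases of patients bringing up the topic of PE with their GP". Statistical methods also speaks of new cases, there of patients suffering from several forms of PE. Neither section defines a new case.

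**Who knows the arm.** Under Allocation, the GP's surgery is the randomised unit and the code is released once the GP has been recruited. Under Blinding, "neither the GPs from the intervention team nor the researchers recruiting the GPs can be blinded to allocation". Control GPs are meant not to know that they are controls, and patients are blinded to their GP's allocation.

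**The concern.** The trial asks whether trained GPs lead more men to raise PE. A man who booked the consultation because of PE has raised it already. His event says nothing about the training, whichever arm he is in.

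That would matter little if both arms enrolled such men at the same rate. The order of events gives no assurance of this. The arm is fixed first, the GP then hears the reason, and the same GP presents the study and sees the outcome. In one arm that GP has just attended a four-hour workshop on PE. A greater readiness to enrol PE presenters there, even without intent, would feed directly into the primary comparison. Intention to treat protects the comparison of the men enrolled. It cannot restore comparability lost when they were chosen.

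**Working it through.** **Step 1: is a PE presenter an event?** PE is a sexual reason, so he is eligible. He has brought up PE with his GP, so he meets the outcome as worded. Reading *new cases* strictly might remove a man already followed for PE, but not one presenting with it for the first time. This is an inference: no section says that he counts, and none says that he does not.

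**Step 2: calibrate the formula.** The article gives no share of PE presenters, so there is no figure of its own to reproduce on this point. The two-proportion formula can be checked on its planning rates (5% v 20%, two-sided 0.05, power 90%):

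n = [1.96 × √(2 × 0.125 × 0.875) + 1.2816 × √(0.05 × 0.95 + 0.20 × 0.80)]² / 0.15² = (0.9167 + 0.5838)² / 0.0225 ≈ 100.1, so 101 per arm.

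This is the article's number 101. The article calls it a total, which is a separate matter and does not enter below.

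**Step 3: effective size.** From the Abstract: 300 patients per arm, losses of 10% (GPs) and 20% (patients), ICC 0.2, 15 patients per GP. After patient losses there are 15 × 0.8 = 12 per GP.

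- Patients left: 300 × 0.9 × 0.8 = 216 per arm
- Design effect: 1 + (12 − 1) × 0.2 = 3.2
- Effective size: 216 / 3.2 = 67.5 per arm

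**Step 4: unequal enrolment with no true effect.** Let q be the share of enrolled men whose stated reason is PE (an assumption), and let 5% of all other men raise PE in both arms. The observed rate is q + (1 − q) × 0.05.

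- Control, q = 2%: 0.02 + 0.98 × 0.05 = 6.9%
- Intervention, q = 8%: 0.08 + 0.92 × 0.05 = 12.6%
- Spurious difference: 5.7 points

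Chance of a significant result favouring the intervention at 67.5 per arm:

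- Null standard error: √(2 × 0.0975 × 0.9025 / 67.5) = 0.0511, times 1.96 = 0.1001
- Standard error under the two rates: √((0.069 × 0.931 + 0.126 × 0.874) / 67.5) = 0.0508
- Φ((0.057 − 0.1001) / 0.0508) = Φ(−0.85) ≈ 0.20

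With equal q the same calculation gives 2.5%, the nominal rate in that direction.

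**Step 5: other assumed splits**, same formula and 67.5 per arm:

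| q control v intervention | Observed rates | False-positive chance |
|---|---|---|
| 2% v 5% | 6.9% v 9.75% | 9% |
| 2% v 8% | 6.9% v 12.6% | 20% |
| 2% v 10% | 6.9% v 14.5% | 30% |
| 5% v 10% | 9.75% v 14.5% | 13% |

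A smaller ICC or no losses raises these figures. For 2% v 8%, all 300 per arm at ICC 0.05 gives an effective 300 / 1.7 = 176.5 and a chance of 44%.

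**Step 6: which handling removes the distortion?** Take 2% v 8% presenters.

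- Presenters kept in the denominator as non-events: 0.98 × 5% = 4.9% v 0.92 × 5% = 4.6% with no effect, and 4.9% v 0.92 × 20% = 18.4% with a true 5% v 20%. The comparison is still disturbed.
- Presenters removed from numerator and denominator: 5% v 5% and 5% v 20%. It is not disturbed by this route.

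**The case against.** The article has safeguards. Inclusion is to be consecutive, an ICPC-2 list guides it, and control GPs are not supposed to know their arm. These stand as mitigation. They do not settle the matter, because no log of eligible men and no comparison of reasons by arm is described, and one arm primed on PE is enough for enrolment to differ.

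A reader might infer that PE presenters also dilute the effect and cost power. The documents do not support that as a loss against plan. Sample size estimation sets the 5% alongside the pilot's control rate of 6.6%, which is a rate among all included men, and nowhere says that PE presenters are left out. If they are already inside the 5% and 20%, planned power is unchanged. With 2% included, the ratio of 4.0 overall would be (0.20 − 0.02) / (0.05 − 0.02) = 6.0 in the other men. That bears on interpretation, not on sample size. Including every man who consults for a sexual reason is also defensible in a pragmatic trial.

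A reader might also infer that selective enrolment is happening. Nothing in the article shows it, and the 2% v 8% split is invented for illustration.

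Finally, the reason for encounter is not among the covariates named in Statistical methods. A final covariate list is commonly left to the analysis plan, so this is no fault in itself. A three-level variable (sexual, urogenital, psychological) would in any case not separate PE presenters from men with other sexual complaints. The Usual care section suggests that the reason may already be recorded.

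**Conclusion.** The point holds as a weakness of eligibility, endpoint wording and enrolment order taken together. As written, the trial appears to count events that the training cannot cause, and it describes no check that they enter both arms equally. It rests on two inferences: that a man whose stated reason is PE meets the primary outcome, and that GPs who know the reason may differ by arm in whom they enrol.

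The direction of the bias, if trained GPs enrol presenters more readily, is towards a false effect. Its size cannot be derived from the article. Over the assumed splits at 67.5 effective patients per arm, the false-positive chance runs from 9% to 30%, against 2.5% with equal enrolment. These figures show what would follow from an imbalance, not that one exists. The point should be addressed. It does not by itself invalidate the trial.

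**What to change.** 1. Record the reason for encounter before consent, with PE as its own category, and record whether the man is already followed for PE.
2. Before unblinding, prespecify an analysis of the primary outcome that removes men whose stated reason was PE, or who are already followed for it, from numerator and denominator. Show it beside the all-patient result. Because recruitment was under way when the article was submitted, adding this analysis is safer than redefining the primary event.
3. Add the reason for encounter as a fixed effect in the adjusted model. With PE as its own level, nearly every man in that level is an event, so a logistic mixed model may not estimate it. The adjusted model is best fitted without those men, using the remaining categories.
4. Report the distribution of reasons by arm as the check for recruitment bias, and state what *new case* means.

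The cost is slightly fewer patients in the added analysis and one case report form field if the reason is not already collected. The limit is that this removes bias only through declared PE presenters. It does not detect selective enrolment of men who gave another reason but seemed likely to raise PE.
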